### Endpoints

#### Primary endpoint

Postoperative complication rates within 30 postoperative days: Postoperative complication rates are calculated as the total number of postoperative complication cases per total operation cases.

Clavien-Dindo grade of postoperative complications in 180 postoperative days: The Clavien-Dindo grade of postoperative complications is evaluated. Only grade III or higher postoperative complications are used for this analysis.

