#### Secondary endpoints

Recurrence-free survival (RFS) in 5 postoperative years: RFS events include locoregional recurrence, distant recurrence, and death by any cause. Contralateral breast cancer and a second primary malignancy are considered to be censored data.

Cancer incidence rate in 5 postoperative years: Cancer incidence rate for those who underwent a prophylactic mastectomy.

Patient satisfaction with reconstruction results preoperative (baseline) and 6 to 12 postoperative months: Reconstruction module with pre- and postoperative scales for satisfaction with the abdomen, as assessed by BREAST-Q version 2.0. (This scale should be completed only by patients who have had reconstruction using a TRAM flap or DIEP flap. Otherwise, it is skipped.) Satisfaction with the back, as assessed by BREAST-Q version 2.0. (This scale should only be completed by patients who have had reconstruction using an LD flap. Otherwise, it is skipped.) Satisfaction with implants, as assessed by BREAST-Q version 2.0. (This scale should only be completed by patients who have had reconstruction using implants. Otherwise, it is skipped.) In all scales, higher scores reflect better outcomes.

Surgeon's satisfaction with surgery within 6 postoperative months: Assessed using scoring criteria for cosmetic assessment [52], response options (overall symmetry, postoperative scar, NAC symmetry, etc.), and range (0–10). Higher scores reflect better outcomes.

Evaluation of the cost-effectiveness of the definitive surgery according to the surgical method: Assessed by conducting a patient’s survey 6 months to 1 year after the last surgery. This evaluation uses the EuroQol five-dimension scale, Korean version questionnaire. In all scales, higher scores reflect better outcomes.

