### Stopping criteria

Patients are free to withdraw from the study at any point without limitation. All data collected before the withdrawal will be included. After a withdrawal, no additional data will be collected from that patient. If the PI determines that it is inappropriate to continue the clinical trial, some part or the entire study could be stopped.

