### Statistical analyses

We have categorized three study sets: Conventional vs. endoscopic, conventional vs. robotic, and conventional vs. endoscopic and robotic. Additionally, subgroup analyses of a randomized registry trial will be conducted to compare the surgical and oncologic outcomes between the conventional and minimally invasive (endoscopic and robotic) groups. Primary and some secondary outcomes (postoperative complications, the satisfaction of patients and surgeons, and the cost-effectiveness evaluation) and other categorical variables will be examined by the chi-square test or Fisher's exact test. Continuous variables will be examined by t-testing or ANOVA and Mann–Whitney testing or Kruskal–Wallis testing, if needed. The other secondary outcomes (RFS, OS, and cancer incidence rates in 5 years) will be examined using Kaplan–Meier plots and log-rank testing. No imputation will be performed for subjects who have missing data due to dropping out of the study. Data relating to major protocol non-adherence due to patients dropping out of the study will be excluded from the analysis population.

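### The two rules on withdrawn patients conflict: one keeps all data collected before withdrawal, the other excludes drop-out data from the analysis population, and applying the exclusion would discard primary outcomes already observed

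*Protocol article*

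**What the plan says.** All references are to the Protocol article.

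- **Stopping criteria.** Patients may withdraw at any time. On their data: "All data collected before the withdrawal will be included". Then: "After a withdrawal, no additional data will be collected from that patient".
- **Statistical analyses.** "No imputation will be performed for subjects who have missing data due to dropping out of the study". The next sentence reads: "Data relating to major protocol non-adherence due to patients dropping out of the study will be excluded from the analysis population".
- **Primary endpoint.** There are two: "Postoperative complication rates within 30 postoperative days" and "Clavien-Dindo grade of postoperative complications in 180 postoperative days", the second restricted to grade III or higher.
- **Secondary endpoints and Statistical analyses.** "Recurrence-free survival (RFS) in 5 postoperative years" is a secondary endpoint. It, overall survival and 5-year cancer incidence "will be examined using Kaplan–Meier plots and log-rank testing".
- **Methods/Design.** Recurrence and survival are to be followed for at least 5 years. The enrolment target is 2000.

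**The concern.** Take a woman who has surgery, completes her day-30 and day-180 assessments, and withdraws in year 2. Under the Stopping criteria her complication outcomes are analysed. Under the exclusion sentence they may not be. Nothing in the article says which rule prevails.

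Three things are at stake:

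- Primary outcomes that were fully observed could be lost because of something that happened later.
- If women with complications leave more often, and this differs between surgical methods, the complication comparison is distorted. The study is not randomised, so this would add to the selection bias that the Discussion already concedes.
- For the 5-year outcomes, the exclusion would use later drop-out to decide who was ever at risk. Kaplan–Meier and log-rank methods normally deal with withdrawal by censoring.

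Two analysts following the article faithfully could reach different results, and a choice made after seeing the data would be data-driven.

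**Working it through.** **1. The plan's one calculated sample size (not disputed).** Pre-specified subgroup analysis gives 112 in total, with rates of 34.8% and 17.1%, margin 0.05, one-sided alpha 0.025 and 80% power. The unpooled formula gives, per arm, (0.348×0.652 + 0.171×0.829) × (1.960 + 0.842)² / (0.05 + 0.348 − 0.171)² = 56.15. Rounded up this is 57 per arm, or 114. Exact enumeration at 56 per arm gives power 0.8004 and alpha 0.0265, which matches the article. If 10% or 20% of a drawn set of 112 were then excluded, approximate power would fall from 80% to 76% or 71%. This loss arises only if the excluded patients are not replaced from the cohort.

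**2. How many known primary outcomes are exposed.** Assumption: a proportion d drops out over 5 years at a constant rate, so the hazard is c = −ln(1−d)/5 per year. The number leaving by day t is 2000 × (1 − exp(−c·t/365.25)).

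For d = 15%, c = 0.0325:
- leaving by day 30: 2000 × 0.00267 ≈ 5
- leaving by day 180: 2000 × 0.01589 ≈ 32
- leaving after day 180: 300 − 32 ≈ 268

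| Assumed 5-year drop-out | Drop-outs of 2000 | Share after day 180 | Number after day 180 |
|---|---|---|---|
| 10% | 200 | 89.7% | 179 |
| 15% | 300 | 89.4% | 268 |
| 20% | 400 | 89.1% | 356 |
| 30% | 600 | 88.5% | 531 |

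About 98% of drop-outs leave after day 30. These are counts of patients. The 30-day rate is defined per operation, so the count of operations would differ somewhat.

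**3. When the complication comparison is biased.** Let a group's risk be r_S in women who stay and r_D in those who leave. The true risk is (1−d)·r_S + d·r_D. After exclusion it is r_S. The error is −d·(r_D − r_S). It is zero if r_D = r_S, and it cancels from the risk difference if it is equal in both groups.

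Illustration with assumed values r_S = 20% and r_D = 40%:
- 15% drop-out: 0.85×20% + 0.15×40% = 23%
- 5% drop-out: 0.95×20% + 0.05×40% = 21%
- after exclusion: 20% against 20%, so a true 2-point difference disappears

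**4. Why no direction can be given for the 5-year outcomes.** Assume a true 5-year event risk of 10%.

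- *Only women who leave event-free are deleted, and withdrawal is independent of events.* With event hazard h = −ln(0.90)/5, estimated RFS is e^(−5(h+c)) / [e^(−5(h+c)) + (h/(h+c))(1 − e^(−5(h+c)))]. At 10% drop-out this is 0.810/(0.810 + 0.095) = 0.895. At 30% it is 0.630/(0.630 + 0.0844) = 0.882. RFS is understated.
- *Everyone who withdraws within 5 years is deleted, including after a recurrence, and withdrawal is independent and continues after recurrence.* The recurrence risk among those left is unchanged. Only deaths, which no withdrawal can follow, leave a residual bias.
- *Everyone who withdraws is deleted, and withdrawal is commoner after recurrence.* Of 1000 women, 100 recur. Suppose 30% of these later withdraw, against 10% of the other 900. The estimate is 70/(70 + 810) = 8.0% against a true 10%. Event risk is understated.

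The same sentence can therefore produce error in either direction or almost none.

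**The case against.** The strongest reply is that the exclusion sentence is narrower than removal of every drop-out. Its subject is data, and it is limited to major non-adherence. The sentence before it rules out imputation for drop-outs with missing values, which would be largely pointless if all drop-outs were deleted. Kaplan–Meier methods also presuppose that withdrawn patients stay in until censored. This stands as a plausible reading, so wholesale removal is one possible reading and not the only one. It does not remove the conflict, because the sentence names dropping out as the cause of the excluded non-adherence and the Stopping criteria allow no exception to inclusion.

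A reader might also infer that drop-outs are necessarily event-free, so that exclusion must overstate event risk. The document does not support this. Recurrence and survival are both followed for at least 5 years, so a woman can recur and withdraw later. A fixed bias in RFS follows only if pre-event drop-outs alone are deleted, which the article does not say.

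It is also fair that the study is exploratory, and that a journal article may leave the definition of major non-adherence to the full protocol or SAP. The missing definition is not the point. The point is that two stated rules disagree.

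**Conclusion.** The conflict is real and should be settled before any comparative analysis. If the exclusion is applied to women who withdraw, it discards primary outcomes already known for nearly nine in ten of them: about 268 of 2000 patients at an assumed 15% constant drop-out over 5 years, and 179 to 531 across 10% to 30%. The certain cost is precision. Bias in the complication comparison is conditional on drop-out being related to complications and differing by surgical method. For RFS, overall survival and cancer incidence the results can be biased, but the direction and size depend on whether drop-outs after an event are also deleted and on drop-out rates that the article does not give. No survival figure above should be read as an expected bias in this study.

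**What to change.** Replace the exclusion sentence in Statistical analyses with wording that agrees with the Stopping criteria:

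- every enrolled, operated patient is in the analysis population;
- complications are analysed on all data observed to day 30 and day 180;
- time-to-event outcomes are censored at withdrawal or last contact, and events recorded before that date are kept;
- any analysis that excludes drop-outs is a defined sensitivity analysis only.

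Censoring does not cure withdrawal that is related to prognosis, so drop-out should be reported by surgical method. The cost is a few sentences in the protocol or SAP, with no extra patients and no new data.

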## Discussion

This study will provide evidence about the surgical outcomes, oncologic outcomes, and patient satisfaction with RNSM and ENSM, compared with CM.

This prospective cohort study has some advantages over previous retrospective studies conducted in a single center or with a single surgeon. The sample size of the study is larger than previously published studies of RNSM. Additionally, our protocol will collect large-scale PRO data about cosmesis after RNSM. The participation of many surgeons from multiple institutions will allow us to observe the effects of different surgeons or institutions on the clinical outcomes of the surgical procedures. In Korea, an increasing number of breast surgeons has been performing RNSM because of active educational programs and systematic research activities. Therefore, the involvement of many skilled surgeons will produce accurate clinical outcomes for the procedures. However, because this is not a randomized controlled trial, selection bias might still occur in determining the surgical modality for each subject. To overcome that limitation and secure the surgical and oncologic outcomes from a new, innovative surgical procedure, we are planning a randomized controlled trial for the near future.

Through this study, we wish to confirm that minimally invasive breast surgery can be considered as a standard treatment for women with breast cancer and as a preventive treatment for women with a high risk of pathogenic variants.

## Data Availability

The datasets used and/or analyzed during the current study are available from the corresponding author upon reasonable request.

## Abbreviations

CM: Conventional mastectomy
CNSM: Conventional nipple-sparing mastectomy
DIEP: Deep inferior epigastric perforators
DTI: Direct-to-implant
EABS: Endoscopic-assisted breast surgery
ENSM: Endoscopic nipple-sparing mastectomy
IBR: Immediate breast reconstruction
KoREa-BSG: Korea Robot-Endoscopy Minimal Access Breast Surgery Study Group
LD: Latissimus dorsi
MARRES: Mastectomy with Reconstruction Including Robot Endoscopic Surgery
NAC: Nipple-areolar complex
NSM: Nipple-sparing mastectomy
OS: Overall survival
OPBC: Oncoplastic Breast Consortium
PI: Principal investigator
PRO: Patient-reported outcomes
QOL: Quality of life
RFS: Recurrence-free survival
RNSM: Robotic nipple-sparing mastectomy
RRM: Risk-reducing mastectomy
SSM: Skin-sparing mastectomy
TRAM: Transverse abdominis rectus muscle
